### FMD measurement

FMD measurements will be performed by professionally trained investigators using the UNEX EF-18VG system (UNEX Corporation, Nagoya, Japan). FMD measurements for the brachial artery will be performed by an experienced cardiologist. Patients’ arms will be immobilized in the extended position, and the brachial artery will be scanned longitudinally 3–5 cm above the antecubital fossa. Baseline measurements for the brachial artery will be recorded, and the cuff will be inflated to 200 mmHg (or 50 mmHg higher than the systolic blood pressure) for 5 min to induce forearm ischemia. Subsequently, the cuff will be deflated, and the diameter of the brachial artery will be measured 60 s after deflation. FMD is defined as the percent change in the diameter of the brachial artery from baseline to post-reactive hyperemia. As a result, FMD will be obtained as a continuous variable. All measurements will be performed by a single investigator who will be blinded to the clinical details.

### ACI measurement

ACI will be measured according to our previous report [11]. In short, the percentage area of the aortic circumference occupied by calcified material will be measured in each sequential consecutive 10-mm slice in non-contrast computed tomography (CT), and the mean percentage of all slices will be calculated for each patient. ACI will be determined by two investigators in separate institutes, and the average of the two values will be used for analysis.

### ESC count

The ESC count will be determined using flow cytometry as previously reported [32]. Fresh peripheral blood mononuclear cells will be obtained by density gradient centrifugation, and cell counting will be performed immediately. The cells will be stained with the following antibodies: Brilliant Violet (BV) 421 mouse anti-human CD34 (IgG1, к), phycoerythrin (PE) CD133 (clone W6B3C1), and Alexa Fluor 637 mouse anti-human CD309 (VEGF-2) antibody. The following isotype control antibodies will be used: BV 421 mouse IgG1, к, PE mouse IgG1, к (clone MOPC-21), and Alexa Fluor (clone MOPC-21) antibodies. After surface staining for 30 min at 4 °C in the dark, the cells will be washed with phosphate-buffered saline solution. Surface-stained cells will be then subjected to fluorescence-activated cell sorting (FACS) using a BD LSRFortessa^TM^ flow cytometer. The ESC frequency will be defined as the number of cells per 10^6^ events for each sample. Based on the surface expression of CD34, CD133, and CD309, ESCs will be determined by flow cytometry and differentiated into four subpopulations, namely CD34^+^, CD34^+^CD133^+^, CD34^+-^CD309^+^, and CD34^+^CD133^+^CD309^+^ cells. These four cell subpopulations will be counted as ESCs as described previously [32].

### Enzyme-linked immunosorbent assay

Serum levels of VEGF (R&D Systems, Inc.; MN), MCSF (R&D Systems, Inc.; MN), 8-OHdG (Japan Institute for the Control of Aging, Nikken Seil Co., Ltd., Shizuoka, Japan), and MDA (ELISAGenie, London, UK) will be determined using enzyme-linked immunosorbent assay (ELISA; R&D Systems, Inc.; MN).

### Cardiovascular diseases, cerebrovascular diseases, and stenosis of blood access

Regarding cardiovascular diseases, new onset of ischemic heart disease and arrhythmia requiring medical treatment will be recorded. With regard to arrhythmia, frequent arterial or ventricular premature beats, supraventricular or ventricular tachycardia, and atrial fibrillation will be evaluated. In addition, the frequencies of hypertension, hypotension, and new-onset arrhythmia will be recorded. Hypertension and hypotension are defined as systemic blood pressures > 160 mmHg and < 80 mmHg, respectively. Cerebrovascular diseases include cerebral hemorrhage, cerebral infarction, and subarachnoid bleeding. Stenosis of blood access is defined as new-onset stenosis requiring balloon dilation and/or surgery.

### Data collection and management

Patients will be identified by a specific number, which will be assigned by independent staff. All clinical data will be collected from patient records. All data and information about this trial will be protected by passwords, and two persons responsible for information control will be able to access the data. In addition, three independent investigators will check the data for accuracy. Data monitoring will be performed according to the research plan approved by the clinical research review board of Nagasaki University. In short, the data management committee consisting of the approved data and information managers in Nagasaki University Hospital who were independent of competing interests and sponsors will oversee the handling of data, including storing and sharing data, every 3 months. To promote participant retention and complete follow-up, information on patients’ conditions and the data will be totalized in the executive office in Nagasaki University Hospital every 3 months. Any outcome data will be collected and listed for participants who discontinue or deviate, at the time of the event. All individual data and biological specimens will be preserved at the Nagasaki University Hospital until analyses. There is no plan to use the residual samples.

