### Primary endpoint

The primary endpoint is the change in FMD before treatment and 24 months after treatment initiation.

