### Secondary and other endpoints

The secondary and other endpoints are as follows.
FMD at 0, 3, 6, 9, 12, 15, 18, and 21 months after treatment initiation.Aortic calcification index (ACI) at 0, 12, and 24 months after treatment initiation.ESC count in the blood at 0, 3, 6, 9, 12, 15, 18, 21, and 24 months after treatment initiation.Serum levels of vascular endothelial growth factor (VEGF), MCSF, 8-hydroxydeoxyguanosine (OHdG), and malondialdehyde (MDA) at 0, 3, 6, 9, 12, 15, 18, 21, and 24 months after treatment initiation.Incidence of cardiovascular diseases, cerebrovascular diseases, and stenosis of blood access during the 24 months.Adverse events of oral intake of RJ.

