### Follow-up

The patients will visit the hospital 3–4 times per week for maintenance HD. The frequency of HD in a week will be determined by medical judgment based on laboratory data, clinical practice, and patient wishes. Similarly, decisions about the contents of HD will be made according to each institution’s policy independent of this trial. There are no relevant concomitant care and interventions that are permitted or prohibited during the trial.

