### Safety management

If serious adverse events (SAEs) that are speculated to be associated with oral RJ intake, RJ administration will be discontinued. In case of the existence of a causal relation between SAEs and RJ, this study will be terminated. Judgments about RJ-related SAEs will be made by medical investigators at each institute and will be reported to the ethics committee within 24 h and to the coordinate centers within 3–5 days (3 working days). If mild adverse events occur, RJ administration will be discontinued until recovery. In this study, changes in drug dose will not be permitted. On the other hand, RJ administration and all examinations will be terminated in case of participant withdrawal. In addition, the principal investigator (YM) must decide to terminate the trial even if one investigator suggests early termination because of SAEs.

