### Statistical analyses

The results of all examinations will be expressed as mean ± SD. To clarify the primary endpoint, the changes in the rates of FMD after treatment for 24 months (FMD for 24 months/baseline) will be compared between the RJ and placebo groups using the Student’s *t* test. Non-adherence and missing data will not be used in this analysis. A similar analysis will be performed to compare the changes in FMD at 6, 12, and 18 months between the two groups. For this analysis, missing data will be used according to the period of RJ administration. Other variables and data will be analyzed similarly at 6, 12, 18, and 24 months. There is no plan for any additional analyses. Permitted investigators (KO, YM, TM, KM) will have access to these interim results.

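### The protocol does not provide for 24-month FMD after a patient stops the product, and the primary test drops such patients, which leaves the comparison open to selection bias

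*Protocol article*

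**What the plan says.** Four parts of the protocol article bear on this point.

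- **Data collection and management**, on participants who stop or deviate: "Any outcome data will be collected and listed for participants who discontinue or deviate, at the time of the event". No later collection point is given for them.
- **Safety management**, on withdrawal: "RJ administration and all examinations will be terminated in case of participant withdrawal". Withdrawal is not defined. The same section separates two other situations. For serious adverse events "speculated to be associated with oral RJ intake, RJ administration will be discontinued", with nothing said about later FMD visits. For mild events the stop is temporary: "If mild adverse events occur, RJ administration will be discontinued until recovery".
- **Primary endpoint** and **Statistical analyses**: "The primary endpoint is the change in FMD before treatment and 24 months after treatment initiation". For the primary t test, "Non-adherence and missing data will not be used in this analysis". The 6-, 12- and 18-month comparisons use missing data according to how long the patient took the product, and no additional analyses are planned.
- **Follow-up** and **Secondary and other endpoints**: "The patients will visit the hospital 3–4 times per week for maintenance HD". One secondary endpoint is "Incidence of cardiovascular diseases, cerebrovascular diseases, and stenosis of blood access during the 24 months".

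The Sample size section expects incomplete data in roughly 20% of patients.

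**The concern.** A superiority trial rests on comparing the groups as randomised. Here the patient's course on the product can decide whether the primary outcome is measured or used. Suspected product-related serious adverse events lead to stopping, so stopping is tied to tolerance and illness, and illness may also affect endothelial function. If patients who stop differ in outcome from those who continue, and the share stopping (or that difference) is not the same in both arms, the completers no longer form a fair comparison. An FMD value that was never taken cannot be recovered afterwards. Much of this loss looks avoidable, because most patients who stop the product will still attend the dialysis unit several times a week.

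**Working it through.** **1. How far the text goes, group by group**

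| Group | Examinations after the event | 24-month FMD in the primary test |
|---|---|---|
| Withdrawal (undefined) | All ended (Safety management) | No: certain |
| Permanent discontinuation or deviation | Only collection at the event is stated (Data collection and management) | No: natural reading, but inferred |
| Non-adherent, still attending | Not said to stop | May be measured, then left out (Statistical analyses) |
| Paused for a mild adverse event | Pause lasts until recovery; patient stays in the trial | Not lost through the pause itself |

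The rule tying the 6-, 12- and 18-month data to time on product supports the inference in the second row.

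**2. The plan's own numbers**

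Inputs from Sample size: 112 per group, alpha 0.05 (taken as two-sided), power 0.80, about 20% incomplete, 135 per group enrolled.

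- 112 × 1.2 = 134.4, rounded up to 135. This reproduces the enrolment figure.
- 20% of 270 = 54 patients without usable data, leaving 135 × 0.8 = 108 per group, slightly under 112.
- The article gives neither effect size nor SD, so 112 cannot be rebuilt directly. Solving the two-sample t test for 80% power at 112 per group gives an implied standardised difference of 0.376.
- Power at 0.376 with 108 per group is 78.5%.

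**3. Bias if the losses are selective**

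Let m₁ and m₀ be the shares lost in each arm, and let lost patients differ from completers by k SD in both arms. With no true effect:

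- bias = (m₁ − m₀) × k
- SE = √[1/(135(1 − m₁)) + 1/(135(1 − m₀))]
- type I error = P(|Z + bias/SE| > 1.96)

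Example: for 25% against 15% and k = 0.5, bias = 0.10 × 0.5 = 0.05 SD. The analysed groups are 101.25 and 114.75, SE = 0.136, bias/SE = 0.367, and type I error = 0.066.

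| Lost (m₁ v m₀) | k | Bias (SD) | Two-sided type I error |
|---|---|---|---|
| 20% v 20% | any | 0 | 0.050 |
| 25% v 15% | 0.25 | 0.025 | 0.054 |
| 25% v 15% | 0.5 | 0.05 | 0.066 |
| 25% v 15% | 1.0 | 0.10 | 0.114 |
| 30% v 10% | 0.25 | 0.05 | 0.065 |
| 30% v 10% | 0.5 | 0.10 | 0.113 |
| 30% v 10% | 1.0 | 0.20 | 0.308 |

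The overall 20% comes from the plan. The split between arms and k are assumptions.

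**4. What continued follow-up does to power**

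Assume half of the 20% stopped the product but can still be measured. Then 135 × 0.9 = 121.5 per group are analysed, of whom 13.5 are off product. If these keep a fraction f of the effect, the average difference is 0.376 × (108 + 13.5f)/121.5.

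| f | Difference (SD) | Power at 121.5 per group |
|---|---|---|
| 1 | 0.376 | about 83% |
| 0.5 | 0.355 | about 79% |
| 0 | 0.334 | about 74% |

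The starting point is 78.5%, so power can rise, stay level or fall.

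**The case against.** The strongest reply is that nothing in the text cancels later FMD visits for patients who discontinue or deviate. Collection at the event could be an extra assessment, and the protocol ends examinations only for withdrawal. This stands in part: loss is a stated rule for withdrawal only. But nothing provides for continued measurement either, and an article that fixes one collection point for these patients invites sites to stop there.

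A reader might infer that anyone who stops the capsules contributes no 24-month FMD. The documents do not support that for patients paused for mild events, nor for non-adherent patients who may be measured and then excluded.

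A reader might also infer that vascular events after stopping go uncounted. No sentence says so. Clinical data come from patient records, these events need no study examination, and the withdrawal rule ends examinations, not record review.

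It may also be said that an article condenses the full protocol. That would excuse silence, but the withdrawal rule, the timing of collection and the exclusion from the primary test are all stated.

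Finally, with equal losses and the same mechanism in both arms there is no bias. That is correct, but nothing in the plan ensures it. Dialysis attendance also gives no access to patients who die or move away, and withdrawn consent may rule out measurement.

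**Conclusion.** The concern holds in this limited form. Withdrawal, undefined, ends all examinations. After discontinuation or deviation, FMD to 24 months is not provided for. The primary test then leaves out non-adherence and missing data. Followed as written, patients who permanently stop the product have no 24-month FMD in the analysis, with certainty after withdrawal and by inference otherwise.

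The consequence is exposure to selection bias, not demonstrated bias. In the scenarios shown, type I error runs from 0.05 (equal losses, same mechanism) to 0.308 (30% against 10%, 1 SD apart). It would be wrong to conclude that the randomised comparison is necessarily lost, or that the fix mainly buys power. The rise from 78.5% to about 83% needs half of the expected losses to be recoverable and the full effect to persist off product. With no persisting effect, power falls to about 74%. The change should be made, because data not collected cannot be restored later.

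**What to change.** 1. **Data collection and management, and Safety management:** define withdrawal and separate stopping the product from withdrawing consent for follow-up. State that stopping the product does not end study participation, and that scheduled FMD, blood sampling and event recording from the dialysis record continue to 24 months unless consent for follow-up is withdrawn. This concerns data collection only and leaves the rules for stopping the product as they are.
2. **Statistical analyses:** have the primary analysis include all randomised patients with a 24-month FMD, in their allocated group and regardless of adherence. Without this, the patients recovered under item 1 could still be removed as non-adherent.

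The cost is an amendment and visits that are already scheduled. The downsides are FMD examinations in patients no longer taking the product and possible dilution of the effect. If follow-up to 24 months is already intended, item 1 is a clarification, but item 2 is still needed.

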### Safety management

If serious adverse events (SAEs) that are speculated to be associated with oral RJ intake, RJ administration will be discontinued. In case of the existence of a causal relation between SAEs and RJ, this study will be terminated. Judgments about RJ-related SAEs will be made by medical investigators at each institute and will be reported to the ethics committee within 24 h and to the coordinate centers within 3–5 days (3 working days). If mild adverse events occur, RJ administration will be discontinued until recovery. In this study, changes in drug dose will not be permitted. On the other hand, RJ administration and all examinations will be terminated in case of participant withdrawal. In addition, the principal investigator (YM) must decide to terminate the trial even if one investigator suggests early termination because of SAEs.

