### Exclusion criteria

The exclusion criteria are as follows.
Patients who already consume RJ or original bee food products.Patients who plan to consume RJ during the trial period.Patients with severe vascular diseases that need treatment.Patients allergic to RJ or original bee food products.Patients with a history of asthma or atopic dermatitis.Pregnant or lactating patients.Patients who are judged as unsuitable for inclusion in the trial by the principal investigator or co-investigators.

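### The mild-adverse-event rule has no exception for suspected allergy, so on its ordinary reading the full dose resumes after a mild reaction to the study product

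*Protocol article*

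**What the plan says.** The Safety management section of the protocol article separates adverse events by seriousness.

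- Serious events suspected to be related to the product: "If serious adverse events (SAEs) that are speculated to be associated with oral RJ intake, RJ administration will be discontinued".
- Mild events, with no qualification by type or cause: "If mild adverse events occur, RJ administration will be discontinued until recovery".
- Dose: "In this study, changes in drug dose will not be permitted".
- Withdrawal: "RJ administration and all examinations will be terminated in case of participant withdrawal".

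The Study design section sets the royal jelly dose at 3600 mg/day for 24 months. The Exclusion criteria bar "Patients allergic to RJ or original bee food products", and also anyone with a history of asthma or atopic dermatitis.

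**The concern.** Allergy to the product is the one product-specific hazard that the protocol screens for at entry. Screening can catch only what is already known. A participant who first shows signs of allergy after randomization, such as a mild rash or itching, falls under the mild-event rule, because the event is not serious. That rule makes no distinction between an itch that points to the study product and an unrelated cold. Read in the ordinary way, it sends both participants back to the full dose on recovery.

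What is at stake is the safety of individual participants: repeated exposure to a suspected allergen, at full dose, for the rest of the 24 months. The error rates of the trial are not in question.

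**Working it through.** The article gives no figure for this point, so the main check is a reading of the sections against each other. Arithmetic enters only in costing the fix.

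**Does the rule imply a restart?**

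1. The mild-event sentence sets an end to the interruption, namely recovery. The serious-event sentence in the same section sets none. The natural reading of the difference is that the first is a pause and the second a stop.
2. Dose changes are not allowed, so a restart is at the assigned dose: 3600 mg/day in the royal jelly arm.
3. The mild-event sentence carries no exception. A mild, non-serious, suspected allergic reaction is therefore inside it and outside the serious-event rule.
4. Had the same allergy been known at screening, the participant would have been excluded. The entry rule and the on-study rule thus treat the same hazard in opposite ways.

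**Who is affected?** Only participants with a new-onset, mild, non-serious reaction. Known allergy, asthma and atopic dermatitis are excluded at entry, and suspected serious reactions already stop product. The article gives no on-study allergy rate, so no count can be derived.

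**What would the fix cost in power?** The Statistical analyses section says of the primary comparison: "Non-adherence and missing data will not be used in this analysis". A participant taken off product may therefore drop out of that comparison.

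Inputs from the Sample size section: 112 per group for 80% power at alpha 0.05, 135 per group enrolled, and incomplete data in about 20%. Assumptions: a two-sided two-sample t test, and the 20% applied as a loss from the 135.

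- Standardised difference implied by 112 per group at 80% power: 0.376.
- Remaining after 20% loss: 135 × 0.8 = 108 per group.

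| Analysed, group 1 vs group 2 | Power |
|---|---|
| 108 vs 108 | 78.5% |
| 107 vs 107 | 78.2% |
| 106 vs 106 | 77.8% |
| 105 vs 105 | 77.4% |
| 107 vs 108 | 78.4% |
| 106 vs 108 | 78.2% |
| 105 vs 108 | 78.0% |

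Losing 3 from each group costs 78.5 − 77.4 = 1.1 points, or about 0.4 for each participant lost per group. Losing 3 from one group only costs 78.5 − 78.0 = 0.5 points, or about 0.2 each. The range of 0 to 3 illustrates a few losses and is not an estimate.

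**The case against.** **Resumption is not written.** The sentence does not say that product must be restarted, when, or on whose decision. The prose is loose (the serious-event sentence lacks a verb), so small differences in wording carry limited weight. Barring dose changes does not require rechallenge. The article elsewhere foresees participants who discontinue or do not adhere, so an investigator may keep someone off product. All of this stands and limits the force of the point. It does not remove it, because a site that simply follows the sentence would restart.

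**An article condenses.** The full protocol is not shown and may hold an allergy-specific stopping rule. That would answer a complaint about silence. Here, however, the article states a rule that covers all mild events, and the rule as stated gives the worse result for this group.

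**Few people are affected, and the product is a commercial supplement at its recommended dose.** This stands and is why the point is minor. A general view that the product is safe still does not settle what to do for a person who appears to react to it.

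**A stronger reading to avoid.** A reader might infer that participants who stop product are also lost to follow-up, so that endpoints such as "Incidence of cardiovascular diseases, cerebrovascular diseases, and stenosis of blood access during the 24 months" are not captured to month 24. The inference would lean on the Data collection and management section: "Any outcome data will be collected and listed for participants who discontinue or deviate, at the time of the event". The article does not support it. That sentence does not say that collection then ends. Examinations are terminated only on participant withdrawal. The same section describes three-monthly collation of data to promote complete follow-up, and these patients attend for dialysis 3–4 times a week.

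**Conclusion.** The point holds as a minor safety correction. On its ordinary reading, the mild-event rule returns a participant with a mild suspected allergic reaction to the full assigned dose, although the protocol treats that allergy as a reason not to give the product.

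This rests on two things: that *until recovery* describes a pause, which is inferred, and that no allergy exception exists in the undisclosed full protocol, which cannot be checked. The number of participants cannot be estimated and is probably small. For each one in the royal jelly arm, the exposure is 3600 mg/day for whatever remains of the 24 months. Neither a loss of month-24 follow-up nor any bias in the primary analysis is shown.

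**What to change.** Amend the Safety management section to say that suspected hypersensitivity to study product, of any severity and in either blinded arm, leads by default to permanent discontinuation of product. Add, for clarity, that this is not participant withdrawal, so scheduled examinations continue, as the section already implies. Leave the present rule in place for other mild events.

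The cost is one or two sentences in a protocol amendment. Because the default applies in both arms, it needs no unblinding. A few participants will come off product and may be left out of the primary analysis as non-adherent, at the small power cost shown above. That is a fair price for not re-exposing someone to a suspected allergen.
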